## Abstract

**Background:**

Leprosy is curable with multidrug therapy and treatment in the early stages can prevent disability. However, local nerve damage can lead to injury and consequently recurring and disfiguring ulcers. The aim of this study is to evaluate the treatment of leprosy ulcers using an autologous blood product; leukocyte and platelet-rich fibrin (L-PRF) to promote healing.

**Methods:**

This is a single-centre study in the Anandaban Hospital, The Leprosy Mission Nepal, Kathmandu, Nepal. Consenting patients (n=130) will be individually randomised in a single-blinded, controlled trial. Participants will be 18 years of age or older, admitted to the hospital with a clean, dry and infection-free chronic foot ulcer between 2 and 20 cm^2^ in size. If the ulcer is infected, it will be treated before enrolment into the study. The intervention involves the application of leukocyte and platelet-rich fibrin (L-PRF) matrix on the ulcer beds during twice-weekly dressing changes. Controls receive usual care in the form of saline dressings only during their twice-weekly dressing changes. Primary outcomes are the rate of healing assessed using standardised photographs by observers blind to allocated treatment, and time to complete re-epithelialization. Follow-up is at 6 months from randomisation.

**Discussion:**

This research will provide valuable information on the clinical and cost-effectiveness of L-PRF in the treatment of leprosy ulcers. An additional benefit is the evaluation of the effects of treatment on quality of life for people living with leprosy ulcers. The results will improve our understanding of the scalability of this treatment across low-income countries for ulcer healing in leprosy and potentially other conditions such as diabetic ulcers.

**Trial registration:**

ClinicalTrials.govISRCTN14933421. Registered on 16 June 2020

## Administrative information

Note: the numbers in curly brackets in this protocol refer to SPIRIT checklist item numbers. The order of the items has been modified to group similar items (see http://www.equator-network.org/reporting-guidelines/spirit-2013-statement-defining-standard-protocol-items-for-clinical-trials/).

## Introduction

### Background and rationale {6a}

Leprosy is a chronic infectious disease that causes neuritis with loss of sensation. Neuropathy is caused primarily by inflammatory episodes called ‘reactions’, which can occur in 30–50% of leprosy cases in response to live *Mycobacterium leprae* or residual antigens persisting for years in skin and nerve tissues after curative treatment [1, 2]. Neuritis can develop and recur at any time before, during or even years after leprosy treatment [3]. The combination of loss of sensation and deformities leads to the presentation of ulcers, often with the first presentation within 4–5 years of leprosy diagnosis, and then an increased lifetime risk of recurrent ulcers, which can lead to deformity and permanent disability.

Nepal, with over 3200 new cases of leprosy annually, is one of 23 priority countries for the World Health Organization’s (WHO) global national leprosy programme [4]. The prevalence rate of leprosy is rising, though this may be due to improved reporting and active case finding [4]. While leprosy is curable with multidrug therapy, Nepalese people may hide early symptoms due to stigma based on cultural perceptions that leprosy is a punishment for former life transgressions [5]. Thus, there are often delays in presentation of leprosy, which can lead to the development of complex ulcers requiring long hospital stays. Furthermore, weight bearing and physical activity are often adversely associated with healing rates of plantar ulcers [6] but resting to prevent or heal an ulcer is impractical for many affected people who need to work to earn their living.

People afflicted with recurrent ulcers suffer severe consequences in terms of loss of function, loss of earnings, stigma, and often severe mental distress [7]. This protocol concerns the evaluation of a promising intervention to promote the healing of leprosy ulcers, and so improve wellbeing and quality of life for people living with leprosy. Findings would also be relevant to other ulcerative conditions, particularly diabetes, where ulcers can similarly result from peripheral nerve damage.

Leprosy ulcers heal slowly, because they are large and/or deep when they present and possibly because the skin is less moist due to damage to autonomic nerves. Slow healing leads to an extended stay in hospital, which has implications for the patients, their family members and for hospitals. Current methods of topical treatment include applications of zinc tape, wax therapy, human amniotic membrane gel, topical phenytoin, saline gel, or emerging cellular therapies such as platelet-rich plasma gel [8, 9]. However, results from intervention studies are ambiguous [8] and recent Cochrane reviews have called for higher quality research on ulcer treatment and prevention in leprosy, specifically advocating for randomised controlled trials (RCTs), ‘blinding’ of outcome measurement and appropriate sample size [8, 10].

Autologous platelet-rich plasma (PRP) is a cellular therapy with the potential to improve the healing of chronic wounds and avoid limb loss [11]. A Cochrane review suggested that it may be beneficial for diabetic patients, although the effect size was modest and the trials were not of high quality [12]. A trial of PRP to promote tendon healing did not find evidence that it was effective [13]. A ‘second generation’ of the treatment, leukocyte and platelet-rich fibrin (L-PRF), shows promise, albeit with inconclusive formal research evidence. Results from one longitudinal study in Chile [14] showed potential with a reduction in the size of wounds and closure of some chronic ulcers. However, patients acted as their own controls and so the cause of the recovery cannot be attributed to any particular aspect of the care. A trial of L-PRF in neuropathic diabetic ulcers also demonstrated positive results although the analysis was not by intention to treat [11].

Irrespective of these inconclusive or null findings, this therapy is currently used in low and middle income (LMIC) countries [14], including Anandaban Hospital, The Leprosy Mission Nepal. The use of the therapy here suggests that the treatment would be scalable if proven effective; however, reliable evidence from a randomised trial is needed to support its continued or expanded use given that it is more costly than conventional therapy.

### Aim and objectives {7}

The aim of this study is to evaluate the efficacy of L-PRF on healing rates for leprosy ulcers, time to healing and duration of hospital stay.

The objectives are as follows:
Recruit 130 eligible adults.Randomise participants to intervention (application of leukocyte and platelet-rich fibrin (L-PRF) matrix on the ulcer beds) or standard care (saline dressings only).Monitor rate of healing based on two observations per week (cm^2^ per unit time).Monitor the time to complete re-epithelialization (up to a maximum of 70 days).Monitor participant activity using a pedometer.Measure health-related quality of life fortnightly using the EQ-5D 3L.Compare the main and secondary end-points between treatment arms.Monitor recurrences of treated ulcers, appearances of new ulcers and any anatomical changes in the limb at follow up (6 months from randomisation).Undertake an economic evaluation to estimate the impact of L-PRF on net population health in terms of daily and quality adjusted life years (DALY/QALYs).

### Trial design {8}

A single-centre, prospective, single blinded, parallel group, 1:1 individually randomised controlled trial. Study duration is 48 months (maximum). Participants and practitioners will not be blinded, but the assessors will be completely blinded, as we describe in the section on ulcer measurements. Each participant will be followed up for up to 6 months from the point of randomisation. Consent (see ethics) and baseline data collection will precede randomisation. A summary of the study pathway is shown in Fig. 1.

**Fig. 1 Fig1:**
[figure not shown]
Summary of study pathway and participant timeline

## Methods: participants, interventions and outcomes

### Study setting {9}

The study will be conducted at the Anandaban Hospital currently run under The Leprosy Mission Nepal. The Anandaban Hospital lies in southern part of Lalitpur district of Nepal, approximately 20 km south of Kathmandu in the Bagmati province. Established in 1957 by The Leprosy Mission England & Wales, it is the tertiary leprosy referral hospital in Nepal, with 110 beds and provides specialist tertiary leprosy care for approximately 6000 patient visits annually from all over Nepal and the Northern part of India. It also provides general medical care for the local population.

### Eligibility criteria {10}

The inclusion criteria are as follows:
Patients with a chronic foot ulcer of at least 6 weeks duration due to leprosy neuropathy≥18 years of age.Ulcer surface area between 2 and 20 cm^2^ inclusive.Ulcer is clean, dry and free from infection.Patient can provide informed consent.

The exclusion criteria are as follows:
Any significant medical condition, laboratory abnormality, or psychiatric illness that would prevent the participants from participating in the study (e.g. diabetes or diabetic ulcer, HIV, chronic Hep B, chronic Hep C or TB patients under active treatment).Ulcer with surface area <2cm^2^ and >20cm^2^.Untreated high blood pressure > 150 mm HG systolicHaemoglobin less than 9 gm/dL or platelets < 100×10^3^/ulPatient requires skin graft.Pregnant or breast-feeding.Patients with Erythema Nodosum Leprosum (ENL) or a leprosy reaction under steroid treatment.Any wound that has clinical microbial infections.A patient who has returned to the hospital having previously been a participant in the trial.

### Who will take informed consent {26a}

A local research fellow trained in Good Clinical Practice (GCP) will screen all admissions for eligibility. Eligible patients will be provided with a Patient Information Leaflet and verbal information as necessary about the study from a research fellow in local languages. Written informed consent will be sought the following day, once eligibility has been confirmed. Thumb or fingerprints will be requested in lieu of a signature if necessary. Translated consent forms have been back-translated according to the WHO methodology [15] for quality assurance purposes.

### Additional consent provisions for collection and use of participant data and biological specimens {26b}

Consent includes the option to give permission for the data collected to be used in future research. Participants can reject this option and still take part in the TABLE trial.

### Intervention

#### Intervention description {11a}

The intervention uses the participant’s own blood to prepare strips of leukocyte and platelet-rich fibrin matrix (L-PRF) to be applied to the ulcer bed. The process is described in detail elsewhere [16] but briefly, up to 80ml of participants’ blood will be collected twice per week at the time of dressing change. The blood will be centrifuged to obtain the fibrin matrix gel, which will be compressed and applied to the ulcer bed and then covered with a Vaseline gauge dressing. Blood collection from participants, centrifugation procedure and application of L-PRF will be done in a minor operating room following aseptic technique. All participants (including those in the control group) will be given iron and folic acid tablets. Both control and intervention groups will receive routine twice-weekly dressing changes by trained nurses or paramedics until their ulcers are healed (complete re-epithelization) up to a maximum of 70 days. Any missed dressing change sessions will be noted but not treated as a deviation from the protocol.

In the event that a participant has more than one ulcer, the largest ulcer will be selected as the index ulcer for analysis purposes before randomisation. However, all of the participant’s ulcers will receive the same treatment. Thus, if the participant is in the intervention group they will receive L-PRF treatment on all of their ulcers. Eligible patients will be offered entry in the trial at the point where their clinician judges them suitable for treatment, i.e., when the lesion is clear of any debris or infection.

#### Activity measurement

All participants will be invited to wear a pedometer (Model: Mi Smart Band 5, Model: XMSH10HM) on the ankle of their non-affected limb (or non-index case affected limb) which they will wear from the first dressing change until 42 days (the point where cross-over may occur) or discharge, whichever comes first. This will act as a proxy measure of weight bearing and enable us to monitor activity across intervention and control groups and thereby evaluate whether the level of activity is similar across groups.

#### Explanation for the choice of comparators {6b}

The comparator is usual care. Participants in the control group will receive usual care of twice-weekly standard saline dressings only and will not have blood taken. The clinical care of these participants will be identical to the intervention participants.

#### Criteria for discontinuing or modifying allocated interventions {11b}

Details of any concomitant illness or medication (present at start of the trial) will be recorded at trial entry. If any change influences the participant’s eligibility to continue in the trial, the local Principal Investigator will be informed and a decision to continue with the intervention will be made in the participant’s best interest. The intervention may also be discontinued at participant’s request. Participants who withdraw will receive usual care.

#### Strategies to improve adherence to intervention {11c}

None.

#### Relevant concomitant care permitted or prohibited during the trial {11d}

Given that weight bearing and physical activity are adversely associated with healing rates of plantar ulcers, all participants will be encouraged to rest during the trial.

#### Provisions for post-trial care {30}

Discharge information will be noted along with the participant and a family member’s contact details. Each trial participant will receive a cell phone and contact details to use in the event of any difficulties. Any readmissions at Anandaban Hospital, or any other hospitals for treatment of the same ulcer (the ‘trial ulcer’), will be recorded (both dates and duration).

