#### Outcomes {12}

The main end-points will be:
‘Rate of healing’ based on two observations per week of ulcer size censored at 42 days (cm^2^ per unit time). We will estimate the effect of the intervention on the change in the ulcer size per unit time, i.e. the rate of healing (see Statistical Analysis).Time to complete re-epithelialization (right-censored at 42 days).

Both end-points will be analysed with and without adjustment for baseline characteristics (trial ulcer area and participants’ age), but we prefer unadjusted outcomes in randomised studies and therefore declare them as ‘primary’.

Secondary end-points:
Rate of healing based on two observations per week up to 70 days (cm^2^ per unit time) (calculated as described below).Time to complete re-epithelisation (observed up to 70 days).Generic quality of life (QoL) measured at first dressing change, fortnightly during in-patient stay and at 6-month follow-up, using the EQ-5D 3L. This scale has previously been used and validated in a Nepali population [17]. As far as we are aware, there is no valuation tariff in the Nepalese population, although this may change by the time that the analysis starts. Therefore, we propose not to prespecify the tariff but instead select the tariff at a later date. We note that tariffs are currently available for nearby countries including Sri Lanka [18] and China [19, 20].Longer-term outcomes measured at 6-month follow-up from randomisation will be proportion with:
i.Recurrence of treated ulcer;ii.Appearance of new ulcer;iii.Anatomical changes in the limb;Days hospitalised prior to discharge and total (to include any readmission due to leprosy/ulcers) by 6 months.Health economic information:
i.Number of visits to any healthcare facility from discharge to the end of follow-up at 6 months.ii.Data on the time taken to change dressings at the twice weekly changes.

Rate of healing will be assessed from blindly assessed photographs (Fig. 2). However, as complete healing may trigger discharge, we will monitor for cases discharged before the blinded assessor in Birmingham has noted complete re-epithelization.

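### The rule for recording readmissions is narrower than the total-hospital-days outcome that it has to supply

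*Protocol article*

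**What the plan says.** Aim and objectives {7} names three things to be evaluated: healing rates, "time to healing and duration of hospital stay". Outcomes {12} turns the last of these into a secondary end-point: "Days hospitalised prior to discharge and total (to include any readmission due to leprosy/ulcers) by 6 months". That definition is limited by cause (leprosy or ulcers) but not by which ulcer or which hospital.

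Provisions for post-trial care {30} states what is recorded after discharge: any readmissions at Anandaban Hospital, "or any other hospitals for treatment of the same ulcer (the ‘trial ulcer’), will be recorded (both dates and duration").

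Three other statements bear on the point:

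- Intervention description {11a}: for a participant with several ulcers, "the largest ulcer will be selected as the index ulcer for analysis purposes before randomisation". The same section adds: "However, all of the participant’s ulcers will receive the same treatment".
- Outcomes {12} lists "Appearance of new ulcer" among the 6-month outcomes.
- Outcomes {12}, under health economic information, lists "Number of visits to any healthcare facility from discharge to the end of follow-up at 6 months".

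**The concern.** An outcome can only be derived from what is collected. Here the outcome includes readmissions for any ulcer and for other leprosy causes, while the rule that supplies dates and durations is tied, at least in part, to one ulcer per participant. The stays at issue are foreseeable. Background and rationale {6a} describes recurrent ulcers and neuritis that can return years after treatment, and new ulcers are themselves a 6-month outcome. Study setting {9} says that patients come from all over Nepal and from northern India, so admission elsewhere is realistic.

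At stake is the completeness of a secondary end-point that carries part of the stated aim. The main end-points, the sample size and the error control are not affected.

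**Working it through.** **1. The two rules side by side.** The trial ulcer is taken to be the index ulcer of {11a}. The sentence in {30} can be read in two ways. Reading A applies the trial-ulcer limit to every hospital. Reading B applies it only to hospitals other than Anandaban.

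| Readmission | Counts under {12} | Recorded, reading A | Recorded, reading B |
|---|---|---|---|
| Trial ulcer, Anandaban | yes | yes | yes |
| Trial ulcer, elsewhere | yes | yes | yes |
| Other or new ulcer, or other leprosy cause, Anandaban | yes | no | yes |
| Other or new ulcer, or other leprosy cause, elsewhere | yes | no | no |

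The last row is a gap on both readings. The health-economic item does not close it, because it is a count of visits and mentions neither days nor reason.

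**2. The plan's own figure.** The planning hazards in Sample size {14} are the only basis for sizing anything, so I first checked that I read them as intended. With 70% and 90% healed by day 42 and constant hazards, HR = ln(0.10)/ln(0.30) = 1.912. Schoenfeld's formula (two-sided 5%, 80% power, 1:1) gives 75 events. The mean event probability is (0.70 + 0.90)/2 = 0.80, so 75/0.80 = 93.75 in total, or 46.9 per group. This reproduces the stated 47.

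**3. Time at risk after discharge.** Follow-up runs from randomisation ({8}), so a shorter first stay leaves more time in which to be readmitted. I assume discharge at healing or at day 70, and 182 days of follow-up.

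- Hazards per day: −ln(0.30)/42 = 0.0287 (control) and −ln(0.10)/42 = 0.0548 (L-PRF).
- Mean first stay, (1 − exp(−70h))/h: 30.2 and 17.8 days, a difference of 12.3 before rounding.
- Time after discharge: 182 − 30.2 = 151.8 and 182 − 17.8 = 164.2 days, a ratio of 1.08. Capping stays at 42 days instead gives 157.6 and 165.6 days, a ratio of 1.05.

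**4. Days outside the rule, if rates per day at risk are equal.** The document gives neither a readmission rate nor a length of stay, so both are assumed: 0.1 to 0.6 readmissions per person-year for causes other than the trial ulcer, and 14 to 60 days each. Days missed = rate × (time after discharge/365) × length of stay, taking reading A so that all such stays are lost.

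| Rate per year | Stay (days) | Control | L-PRF | Difference |
|---|---|---|---|---|
| 0.1 | 14 | 0.58 | 0.63 | 0.05 |
| 0.3 | 30 | 3.74 | 4.05 | 0.30 |
| 0.6 | 60 | 14.97 | 16.19 | 1.22 |

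The level lost in each arm could be appreciable. The between-arm difference is at most 1.22/12.3, about 10% of the difference in first stay, and in the middle row 0.30/12.3, about 2%.

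**5. If rates are not equal.** The sign turns easily. A rate per day at risk that is 7.5% lower with L-PRF (1 − 151.8/164.2 = 0.075) cancels the longer exposure, and anything lower reverses it.

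**The case against.** The strongest reply is that this is loose wording in an article that condenses a fuller protocol. The sentence sits under post-trial care rather than data collection. Its comma allows the reading that all readmissions at Anandaban are recorded. Anandaban is described as the national tertiary leprosy referral hospital, so many readmissions would go there. Plans for assessment and collection of outcomes {18a} provides a 6-month visit at which other stays could be asked about. The schedule figure and the data forms are not shown.

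Most of this stands as a limit on what may be claimed, and it rules out several stronger inferences:

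- **That only trial-ulcer readmissions are recorded anywhere.** This is one of two readings.
- **That the outcome is undercounted.** With the forms unseen, this is a risk and not an established result.
- **That the loss favours L-PRF.** The longer time at risk points that way only if rates are equal. All of a participant's ulcers receive the allocated treatment, so an effective treatment could also lower readmission for non-index ulcers. Possible cross-over at 42 days complicates the comparison further, and the 70-day limit is stated for dressing changes, not for hospital stay.
- **That most of the expected saving could be lost.** If 10% to 30% of participants had a 30-day stay outside the rule, 3 to 9 days per participant would be missing, and a reader might set that against the 12-day difference. But this is a loss within each arm. Only the between-arm part biases the difference, and with 8% more exposure that is about 0.24 to 0.72 days.
- **That the economic model is affected.** The economic evaluation section does not name hospital days as an input.

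The reply does not remove the mismatch. The article does state a recording rule, and on either reading that rule does not cover what its own outcome includes.

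**Conclusion.** The point holds as an inconsistency between {30} and {12}. The outcome counts stays for other ulcers and other leprosy causes at any hospital. The recording rule omits such stays at other hospitals on either reading, and at Anandaban as well on the stricter one. Total hospital days by 6 months therefore risk being undercounted.

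How much bias this puts into the comparison, and in which direction, cannot be determined from the document. Under equal readmission rates per day at risk, discharge at healing or day 70, and the assumed rates and lengths of stay, it is roughly 1 day or less against about 12. The fault concerns one secondary end-point. It is worth correcting because that end-point is part of the stated aim and because days in other hospitals are hard to recover later.

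**What to change.** Reconcile the two sections by amending Provisions for post-trial care {30}. Record every readmission to any hospital from discharge to the 6-month visit, with admission and discharge dates and a reason: trial ulcer, other treated ulcer, new ulcer, other leprosy cause, or other. Derive the outcome in {12} from that record by taking all leprosy and ulcer reasons, and keep trial-ulcer readmissions as an identifiable subset.

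The cost is one extra field on the readmission form and one question at a visit that is already planned. No additional visit or procedure is needed, and the sample size and main end-points are unchanged.
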